## 8.6 Corrective Measures

Corrective measures considered as important for the protection of the health and safety of the study subjects can and should of course be taken immediately by the sponsor and the investigators.

## 8.7 Safety variables

According to the current local regulation:

- An "Annual Safety Report"/"Development Safety Update Report", containing all safety issues linked to the study product (including control product) must be sent each year to EC and Competent Authorities.

# 9 Early termination or suspension of the investigation

The study will be discontinued if the investigators judge it necessary for any reason. Possible scenarios are:

- >50% SAE possible related to the study device
- Technical issues with the study device

If the investigation is terminated prematurely or suspended, the IEC and the competent

authority will be informed promptly and provided with the reason(s) for the termination or suspension by the sponsor-investigator.

## **10 Deviations from the clinical investigation plan**

The Investigator is not allowed to deviate from the CIP, unless in emergency circumstances, where deviations from the CIP protect the rights, safety and well-being of the subjects. Such deviations may precede without prior approval of the competent authority and the IEC, but will be documented and reported to the sponsor and the regulatory authorities as soon as possible.

## **11 Amendments to the clinical investigation plan**

Deviations should be reviewed to determine the need to amend the CIP or to terminate the investigation.

The IEC and competent authority must be informed about any amendment to the CIP.

Any change or addition to this protocol requires a written protocol amendment that must be approved by the investigator before implementation. Amendments affecting the safety of subjects, the scope of the investigation or the scientific quality of the study, require additional approval of the IEC.

Examples of amendments requiring such approval are:

A significant change in study design (e.g. deletion of a control group)

An increase in number of invasive procedures to which subjects are exposed

Addition or deletion of a test procedure for safety monitoring

## **12 Regulatory issues**

This study will be conducted in compliance with the CIP, the current version of the Declaration of Helsinki, the European Directive on medical devices 93/42/EEC, the EN-ISO Norm 14155, EN-ISO 14971 as well as all national legal and regulatory requirements ([29](#), [30](#)).

### **12.1 Ethics approval**

The Sponsor-Investigator will obtain approval from the Independent Ethics Committee before starting the clinical investigation.

### **12.2 Regulatory Approval**

The Sponsor-Investigator will obtain approval from competent authority before starting the clinical investigation.

### **12.3 Consent**

The current study involves a population of vulnerable patients. Patients with septic shock may need emergency interventions including sedation for intubation before the study participation can be discussed. Patients with septic shock often present with confusion and are not judicious. In these situations, in which the patient is not capable to decide to participate or not, the relatives are asked about the presumptive will (advance directive). In all patients, an independent doctor assures the medical treatment with his signature. In all patients, written informed consent from the patient himself will be obtained, once the patient is judicious. This will usually take several days to weeks. The right of the patient to refuse to participate will be respected without giving reasons. Data obtained will be destroyed, except data for security

reasons, which have to be stored by law (EN ISO 14155). Because the data obtained can also influence the security of other patients treated with the medical device within studies or not, their interest of security is rated above the right of the individual patient involved in the study. After finishing the study these data are not stored in the study records but in the patient's medical history record. In the study record a key to the medical history record will be deposited.

If the patient remains not judicious, the consent of a previous nominated legal representative by the patient gives consent according to 'Kantonalem Patientengesetz § 29 Abs. 4 and the Erwachsenenschutzrecht ZGB Art 377 ff' (31).

In a minority of cases, the patient will be conscious and capable to decide to participate or not. In these cases, consent to enter the study will be sought from each subject after a full explanation has been given, an information leaflet offered and time allowed for consideration. Signed informed consent will be obtained. The right of the patient to refuse to participate will be respected without giving reasons. With the signature of an independent doctor, the medical treatment is assured.

After the subject has entered the study the clinician remains free to give alternative treatment to that specified in the CIP at any stage if he/she feels it is in the subject's best interest, but the reasons for doing so should be recorded. In these cases, the subject remains within the study for the purposes of follow-up and data analysis. All subjects are free to withdraw at any time from the CIP treatment without giving reasons and without prejudicing further treatment.

## **13 Statistical considerations**

As mentioned, the endotoxin activity is not well described in the literature, which makes a sample calculation difficult. Therefore, this trial was designed as a pilot study analysing 30 patients in order to collect data enabling an accurate design of future investigations. Dependent and independent continuous variables will be compared using Wilcoxon and Mann-Whitney, respectively. In cases of serial measures repeated measures statistics will be applied. For multiple comparisons overall tests will be used: ANOVA for continuous variables and Kruskal-Wallis tests for ordinal scaled variables. Categorical data will be compared using Fisher's exact and  $\chi^2$  test. The normal distribution of study variables will be confirmed using Kolmogorov-Smirnov test. A P value < 0.05 will be considered statistically significant. To obtain adjusted differences in outcomes for the two study populations, logistic regression will be performed to control for factors or confounders that are significantly different ( $p < 0.05$ ) between compared groups. Data will be analysed using the Statistical Package for Social Sciences (SPSS Windows, version 19.0; SPSS Inc., Chicago, IL).

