### **6.2 Secondary objectives**

The secondary objectives of the study comprise the effects of the two blood purification treatments on cytokine and HMGB-1 removal, haemodynamics, safety, and outcome.

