### **6.4 Secondary endpoints**

The secondary endpoints are the following:

- Measurement of IL-6 and HMGB1 T0 i.e. patient inclusion, at T24 hours, T48 hours, and T 72 hours after treatment initiation;
- Routine measurements of norepinephrine dose, inotropic score, and vasopressor dependency index T0, T24, T48 and T72;
- Haemodynamics: MAP, CVP, HR, CO, ELWI, PVPI T0, T24, T48 and T72
- Routine measurements of volume requirement T0, T24, T48 and T72;
- Routine measurements of ventilation parameters PO2/FiO2, SvO2 T0, T24, T48 and T72;
- Urine output (ml/d)
- Lactate, procalcitonin and pH measurements at T0, T24, T48 and T72 after treatment initiation;
- SOFA score calculation at T0, T24, T48 and T72 ;
- Incidence of renal failure, ICU length of stay
- Patient survival at D28;
- Recording of AEs/SAEs

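### The unrestricted P < 0.05 rule covers 19 unranked serial secondary variables, so with no device effect about 4 to 6 trials in 10 would call at least one significant, and more if several tests per variable are read

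*Protocol*

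**What the plan says.** Section 13 of the protocol gives a single decision rule, "A P value < 0.05 will be considered statistically significant", and attaches it to no particular endpoint. Three further sentences bear on how many tests are read:

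- Three-arm comparison: "For multiple comparisons overall tests will be used: ANOVA for continuous variables and Kruskal-Wallis tests for ordinal scaled variables".
- Repeated measurements: "In cases of serial measures repeated measures statistics will be applied". The term to be tested (group, group by time, or each time point) is not given.
- Two-sample tests: "Dependent and independent continuous variables will be compared using Wilcoxon and Mann-Whitney, respectively". Nothing makes a Mann-Whitney test conditional on a significant overall test.

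Section 6.3 names one primary endpoint, endotoxin activity at 72 hours. The secondary objectives in section 6.2 are broad: "the effects of the two blood purification treatments on cytokine and HMGB-1 removal, haemodynamics, safety, and outcome". Section 6.4 then lists many serial variables, for example "Measurement of IL-6 and HMGB1 T0 i.e. patient inclusion, at T24 hours, T48 hours, and T 72 hours after treatment initiation" and "Haemodynamics: MAP, CVP, HR, CO, ELWI, PVPI T0, T24, T48 and T72", and gives none of them precedence. The purpose of the sample is stated in section 13: "this trial was designed as a pilot study analysing 30 patients in order to collect data enabling an accurate design of future investigations".

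**The concern.** The overall test deals with three arms within one variable, and repeated-measures analysis deals with several times within one variable. Neither deals with the number of variables. Each secondary variable therefore gets at least one chance to cross 0.05, and the protocol does not say which variable should carry the conclusion on cytokines or on haemodynamics.

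What is at stake is the use made of the pilot. A marker that reaches significance by chance among 19 is a natural candidate for the endpoint, or the assumed effect size, of the later trial that this one is meant to inform.

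**Working it through.** The protocol states no power or family-wise error figure, so there is none to reproduce. The only arithmetic, 3 groups × 10 patients = 30, agrees.

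**Step 1: count the serial secondary variables (section 6.4).**

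| Group | Variables | Number |
|---|---|---|
| Mediators | IL-6, HMGB1 | 2 |
| Vasopressor measures | norepinephrine dose, inotropic score, vasopressor dependency index | 3 |
| Haemodynamics | MAP, CVP, HR, CO, ELWI, PVPI | 6 |
| Volume | volume requirement | 1 |
| Ventilation | PO2/FiO2, SvO2 | 2 |
| Urine output | no times in 6.4, but recorded at Visits 2 to 5 (sections 7.9.2 to 7.9.4) | 1 |
| Laboratory | lactate, procalcitonin, pH | 3 |
| SOFA | total score | 1 |
| **Total** | | **19** |

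The synopsis names only 11 of these. Renal failure, ICU stay, survival and adverse events are left out of the count.

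**Step 2: bound under independence.** With k independent tests at 0.05 and no effect, the chance of at least one P < 0.05 is 1 − 0.95^k.

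- One test per variable: 1 − 0.95^19 = 0.62.
- Two tests per variable: 1 − 0.95^38 = 0.86.
- Three tests per variable: 1 − 0.95^57 = 0.95.

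Reaching 0.70 takes about ln 0.30 / ln 0.95 = 23.5 tests, and reaching 0.90 takes about ln 0.10 / ln 0.95 = 44.9. Nineteen single tests cannot reach 7 in 10.

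**Step 3: allow for correlation.** The protocol gives no correlations, so they are assumed: 0 to 0.7 between variables and 0.3 to 0.9 between times. Whenever the between-variable correlation is above 0, the three vasopressor measures are set at 0.9 with each other. Null trials were simulated with normal data, 3 × 10 patients, 19 variables and 3 post-baseline times, 3000 trials per setting. Each cell is the proportion of null trials with at least one P < 0.05; ranges run over the between-time correlations.

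| Between-variable correlation | One overall test per variable | Group and group-by-time | Overall test at each of 3 times | Three ungated pairwise tests on the patient mean |
|---|---|---|---|---|
| 0 | 0.63–0.64 | 0.85–0.87 | 0.83–0.94 | 0.91–0.92 |
| 0.1 | 0.57–0.60 | 0.82–0.85 | 0.79–0.92 | 0.89–0.90 |
| 0.3 | 0.51–0.53 | 0.77–0.78 | 0.71–0.88 | 0.83–0.85 |
| 0.5 | 0.42–0.43 | 0.66–0.67 | 0.60–0.79 | 0.72–0.74 |
| 0.7 | 0.30–0.31 | 0.51–0.52 | 0.46–0.64 | 0.56–0.58 |

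Up to correlation 0.5, the three multi-test layouts lie mostly between 0.66 and 0.94. The lowest value, 0.60, needs correlation 0.5 between variables and 0.9 between times.

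**Step 4: which row is plausible.** Independence is only an upper bound. Section 7.8.3.2 computes the inotropic score from catecholamine doses, including noradrenaline, and the vasopressor dependency index from the inotropic score and MAP. Its SOFA table uses PaO2/FiO2, MAP and catecholamine doses. Several of the 19 are therefore functions of others.

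**Step 5: the primary endpoint.** One overall test of 72-hour EAA holds its 5% level. If the three Mann-Whitney comparisons were instead read without that gate, the chance of at least one false result on the primary would be about 10%. Gated by the overall test it is about 4 to 5%.

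**The case against.** The strongest reply has four parts.

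- **Times are provided for.** Section 13 prescribes repeated-measures statistics, so a reader who multiplies 19 variables by three times and speaks of 57 tests goes beyond the text. This stands. Separate tests at each time are one layout that the wording leaves open, not one it orders.
- **The size depends on the layout.** A reader might infer that 7 to 9 null trials in 10 would show a false secondary result. Section 13 does not support that figure without qualification: it needs two or more tests per variable and correlations no higher than about 0.5. With one overall test per variable, about 6 in 10 is the ceiling. This also stands.
- **The trial has a deciding variable.** A reader might infer that the protocol names none. Section 6.3 names one endpoint at one time; precedence is lacking only within the secondary set.
- **This is pilot work, and detail belongs in the analysis plan.** Unadjusted secondary testing is common in pilots, and the protocol nowhere says that a significant secondary result proves an objective or selects the next endpoint. That lowers the consequence. It does not remove the point, because the significance rule is written in the protocol, without restriction. The concern is with that stated rule, not with detail left to a later document.

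**Conclusion.** The concern holds in a limited form. Section 13 attaches the words statistically significant to any of 19 unranked secondary variables at an unadjusted 0.05. With no device effect and 10 patients per group, at least one such label would appear in about 4 to 6 trials in 10 under the mildest layout, or about 3 in 10 at between-variable correlation 0.7. If group-by-time effects, each time point or ungated pairwise tests are also read, the figure is about 7 to 9 in 10 at correlations up to 0.5, and 5 to 6 in 10 at 0.7.

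These figures rest on assumed correlations, normal data and complete groups of 10. Every case examined is several times the nominal 5%. The primary analysis is sound provided it is judged by its overall test. The change is worth making as an inexpensive improvement; the point does not invalidate the trial.

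**What to change.** Replace the significance sentence in section 13 with:

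> P < 0.05 will be considered statistically significant only for the overall three-group comparison of EAA at 72 h; pairwise comparisons are tested only if it is significant. All section 6.4 variables are exploratory and will be reported as between-group differences with 95% confidence intervals and within-group SDs, without significance claims; the intervals are not adjusted for multiplicity and will not be used to declare an effect.

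The last clause matters: without it, picking out the unadjusted intervals that exclude zero would recreate the same false leads. Differences and SDs are also what the design of a later trial needs.

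The cost is a few sentences, with no new data, patients or procedures. The downside is that secondary results can no longer be called statistically significant.

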## **14 Data Quality Control and Quality Assurance**

### **14.1 Routine Monitoring**

Regular monitoring visits at the investigator's site prior to the start and during the course of the study will help to follow up the progress of the clinical investigation, to assure utmost accuracy of the data and to detect possible errors at an early time point.

CRFs, progress notes and copies of laboratory and medical test results will be available for monitoring. The monitor will review all or a part of the CRFs and written informed consents.

The study will be monitored regularly by an independent monitor according to a pre-defined

monitoring plan.

The monitor will verify that compliance with the CIP is maintained. Any deviation from the CIP will be discussed with the clinical investigators and documented as well as reported to the sponsor.

During monitoring visits, completeness and correctness of the data in the case report forms as well as consistency with the source data will be verified and include following information:

- Patient's informed consent obtained prior to the start of the study, if applicable. Exceptions see section 6.3
- Number of patients enrolled, included, withdrawn or completed
- Verification of source data
- Compliance with inclusion and exclusion criteria
- Compliance with sampling procedures
- Potential deviation from protocol
- Safety issues (i.e. potential observed AEs, SAEs)

## **14.2 Audits and Inspections**

A quality assurance audit/inspection of this study may be conducted by the competent authority or IEC, respectively. The quality assurance auditor/inspector will have access to all medical records, the investigator's study related files and correspondence, and the informed consent documentation that is relevant to this clinical study.

The investigator will allow the persons being responsible for the audit or the inspection to have access to the source data/documents and to answer any questions arising. All involved parties will keep the patient data strictly confidential.

## **15 Data Handling and Record Keeping**

The investigators will use paper case report forms (CRF), one for each enrolled study participant, to be filled in with all relevant data pertaining to the subject during the study. All subjects who either entered the study or were considered not-eligible or were eligible but not enrolled into the study additionally have to be documented on a Screening log. The investigator will document the participation of each study subject on the Enrolment Log.

All information in the paper CRF will be completed in a neat legible manner with a BLACK or a BLUE BALL POINT pen to ensure clarity of reproduced copies in the CRF. All corrections in the paper CRF will be made in a way to not obscure the original entry. The correct data will be inserted, dated and initialled by the investigator. Data that are not available or not done will be made clear by adding NA or ND. CRFs will be kept current to reflect subject status at each phase during the course of study. Subjects are not to be identified in the CRF by name. Appropriate coded identification (Subject Number) will be used.

It will be assured that any authorised person, who may perform data entries and changes in the CRF, can be identified. A list with signatures and initials of all authorised persons will be filed in the study site file and the trial master file, respectively. The defined Dataset will contain all data of the study, and is only accessible by defined persons involved in the study and secured by a password. Changes in the Dataset will be marked with the initials of the designed investigator staff. A declaration ensuring accuracy of data recorded in the case

report form will be signed by the investigator.

Documented medical histories and narrative statements relative to the subject's progress during the study will be maintained. These records will also include the following: originals or copies of laboratory and other medical test results (e.g. ECGs, EEG, x-ray reports) which must be kept on file with the individual subject's CRF. If source data is available on a print out (e.g. laboratory values, x-ray reports), this print out is to be kept in a source data folder, and the data necessary for the study is to be transferred to the CRF.

Essential documents must be retained for at least 10 years after the regular end or a premature termination of the respective study (VKlin Art. 25). Any patient files and source data must be archived for the longest possible period of time according to the feasibility of the investigational site, e.g. hospital, institution or private practice.

## **16 Confidentiality**

Data generation, transmission, archiving and analysis of personal data within this study, strictly follows the current Swiss legal requirements for data protection. Prerequisite is the voluntary approval of the subject given by signing the informed consent prior start of participation of the clinical trial.

Individual subject medical information obtained as a result of this study is considered confidential and disclosure to third parties is prohibited. Subject confidentiality will be further ensured by utilising subject identification code numbers to correspond to treatment data in the computer files.

Such medical information may be given to the subject's personal physician or to other appropriate medical personnel responsible for the subject's welfare, if the patient has given his/her written consent to do so.

Data generated as a result of this study are to be available for inspection on request by the monitors, by the IEC and the competent authorities.

## **17 Insurance**

Insurance is covered by "Haftpflichtversicherung für den Kanton Zürich betreffend das UniversitätsSpital Zürich" (Policy no: 14.970.888).

Any damage developed during the course of the study is covered by this insurance. So as not to forfeit their insurance cover, the subjects themselves must strictly follow the instructions of the study personal. Subjects must not be involved in any other medical treatment without permission of the principal investigator (emergency excluded). Medical emergency treatment must be reported immediately to the investigator. The investigator must also be informed instantly, in the event of health problems or other damages during or after the course of study treatment.

The investigator will allow delegates of the insurance company to have access to the source data/documents as necessary to clarify a case of damage related to study participation. All involved parties will keep the patient data strictly confidential.

A copy of the insurance certificate will be placed in the Investigator's Site File.

## **18 Funding**

Gambro Company is funding this study with an unrestricted grant of 150'000 CHF.

## **19 Study Registration**

The study is/will be registered in the local trial registry of the University Hospital Zürich („Studienregister USZ“). The study will also be registered at trials.gov.

## **20 Publication policy**

After the statistical analysis of this trial the sponsor will make every endeavour to publish the data in a medical journal.

